# Protocol summary

Title: Safety and efficacy of methylene blue combined with artesunate or amodiaquine for malaria treatment in children of Burkina Faso: a pilot study in the frame of the A8 Project of the SFB 544

Design: Single-centre, randomized controlled study in children with uncomplicated falciparum malaria in the Nouna Health District, north-western Burkina Faso

Phase: Phase II

Objectives: The primary objective of this trial is to study the safety of the combination methylene blue (MB)-artesunate (AS) and MB-amodiaquine (AQ) given over three days in 3-4 years old children with uncomplicated falciparum malaria in an area of high malaria transmission intensity compared to the safety of a three days AS-AQ regimen. Secondary objectives are to investigate the efficacy of MB-AS and MB-AQ.

Population: Children aged 3-4 years with uncomplicated malaria from Nouna town.

Sample size: N= 180 (n=60 for each group).

Treatment: The participants in the MB-AS group will receive orally twice daily 10mg/kg MB combined with once daily 4mg/kg AS over 3 days. The participants in the MB-AQ group will receive orally twice daily 10mg/kg MB combined with once daily 10mg/kg AQ over 3 days. The participants of the comparator group will receive a 3 day regimen of once daily oral AS (4mg/kg) combined with once daily AQ (10mg/kg).

Endpoints: The primary endpoint is the number of adverse events (AE) after drug intake until day 28. Secondary endpoints are the number of serious adverse events (SAE), adequate clinical and parasitological response (ACPR) rate on day 28, clinical and parasitological failure rates on day 3, 7, 14 and 28, changes in haemoglobin/haematocrit until day 28, and fever and parasite clearance time.

Study duration and dates: The study will be implemented during the rainy season of the year 2006 (July - October).

# Flow chart for study treatments

Day 0

Day 1

Day 2

Day 3

Day 4

Day 7

Day 14

Day 28

**Blood sample**

**Blood sample**

**Blood sample**

**Blood sample**

**Blood sample**

Inclusion/Exclusion

Informed Consent

Treatment 1

**Examination 1**

**Blood sample**

Treatment 2

Treatment 3

**Examination 2**

Treatment 6

**Examination 4**

Treatment 4

**Examination 5**

**Examination 7**

**Examination 6**

Treatment 5

**Examination 3**

3 days regimen MB-AS or MB-AQ or AS-AQ

# Abbreviations

| MB | Methylene Blue |
| --- | --- |
| AS | Artesunate |
| AQ | Amodiaquine |
| SAE | Serious adverse event |
| AE | Adverse event |
| SSA | Sub-Saharan African |
| CRF | Case Report Form |
| CRSN | Nouna Health Research Centre |
| ACPR | Adequate clinical and parasitological response |
| ETF | Early treatment failure |
| LCF | Late clinical failure |
| LPF | Late parasitological failure |

# Definitions

| Term | Definition |
| --- | --- |
| Baseline values | Directly after the written informed consent a blood sample will be taken for the baseline measurements (laboratory baseline values). |
| Age | The age is calculated using the date of informed consent and date of birth. If the day of the birth date is unknown, it is set to 15. If day and month are missing the 1st of July is considered as the date of birth. |
| D0, D1, D2, D3, D7, D14 and D28 | For the definition of days the latest WHO Definition is used (WHO 2003).  D0= calendar day of the first treatment, D1= first calendar day after the calendar day of first treatment. This definition is used for the endpoints ETF, LCF, LPF, ACPR and fever or parasite clearance time. D7, D14, D28 is defined as the 7th, 14th and 28th day after first drug intake, with a tolerance of –1 and +3 days. |
| ETF | - Danger signs or severe malaria on D1, D2 or D3 + parasitemia - Parasitemia on D2 > D0 count irrespective of axillary temperature - Parasitemia on D3 ≥ 25% of count on D0 |
| LCF | - Development of danger signs or severe malaria after D3 in the presence of parasitemia, without meeting any of the criteria of ETF - Presence of parasitemia + axillary temperature ≥37.5°C on any day from D4 to D28, without previously meeting any criteria of ETF |
| LPF | - Presence of parasitemia on any day from D7 to D28 + axillary temperature <37.5°C, without previously meeting any of the criteria of ETF |
| ACPR | - No parasites on D28 irrespective of axillary temperature without previously meeting any of the criteria of ETF, LCF or LPF |
| Fever clearance | Time between fever at inclusion and first temperature < 37.5°C |
| Parasite clearance | Time between inclusion and time where no more parasites are detectable |
| Recrudescence | Re-emerging of the same *P. falciparum* strain from D14 to D28 according to PCR genotyping |
| Reinfection | New infection from D14 to D28 according to PCR genotyping |
| AEs | The adverse event (=AE) defined in chapter 12 is used, but blue urine is expected for all children in the MB-AS and MB-AQ treatment groups. Only AEs after initiation of study treatment will be tabulated. |
| SAE | The definition of serious adverse event (SAE) is given in chapter 11 |
| Haemolysis | Any drop in haemoglobin (Hb) of >2.5 g/dl within 24 hours |
| Severe acute haemolysis | Hb  5 g/dl or received blood transfusion according to clinical judgement of study physician. |
| Severe acute neurological disorder | Acute change in consciousness   2 convulsions |

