# Assessment of secondary endpoints

Specification of parameters

- Number and proportion of patients with at least one serious adverse event:
  1. acute haemolysis (definition: haemoglobin  5 g/dl and haematocrit  15%, or received blood transfusion according to clinical judgement of study physician)
  2. Other serious adverse events (definition below)
- ACPR will be determined according to the standard WHO protocol (WHO 2003)
- Clinical and parasitological failure rates on day 3, 7, 14 and 28 will be determined according to the standard WHO protocol (WHO 2003)
- Time between inclusion and disappearance of fever
- Time between inclusion and clearance of parasites
- Change in the haematocrit after 2, 3, 7, 14 days and 28 days compared to baseline

Methods of data collection

The following laboratory methods will be employed:

Haematocrit will be measured with a centrifuge. Parasites will be diagnosed with standard techniques by light microscopy. Differentiation of recrudescences from new infections will be achieved by comparing PCR-generated *msp1* and *msp2* genotype patterns in matched pairs of isolates obtained on admission and precisely on the day of reappearance of parasitaemia.

Adverse event (AE) definition

The term “adverse event” covers any sign, symptom, syndrome, illness that appears or worsens in a subject during the period of observation in the clinical trial and that may impair the well-being of the subject. The term also covers laboratory findings or results of other diagnostic procedures that are considered to be clinically relevant.

No causal relationship with the study medication is implied by the use of the term “adverse event”. Adverse events fall into the categories non-serious and serious.

Serious adverse event (SAE) definition (GCP)

A serious adverse event is defined as any untoward medical occurrence at any dose:

(1) results in death (2) is life-threatening (3) requires inpatient hospitalisation or prolongation of existing hospitalisation (4) results in persistent or significant disability/incapacity (5) is a congenital anomaly / birth defect
(“Life-threatening” refers to an event in which the patient was at risk of death at the time of the event; it does not refer to an event which hypothetically might have caused death if it was more severe.)

Classification of severity

Mild: The adverse event does not interfere with the routine activities. The patient may experience slight discomfort.

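### The listed failure criteria leave a gap on D3: a child who is febrile and parasitaemic, with a count below 25% of D0, meets none of them and can end as ACPR

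*Protocol*

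**What the plan says.** The Definitions section of the protocol lists three ways to be an ETF:

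- The clinical route reads "Danger signs or severe malaria on D1, D2 or D3 + parasitemia".
- The rule for a count that falls too little reads "Parasitemia on D3 ≥ 25% of count on D0".
- The rule for a count that rises reads "Parasitemia on D2 > D0 count irrespective of axillary temperature".

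LCF has two routes. One is "Development of danger signs or severe malaria after D3 in the presence of parasitemia"; the other is "Presence of parasitemia + axillary temperature ≥37.5°C on any day from D4 to D28". LPF is "Presence of parasitemia on any day from D7 to D28 + axillary temperature <37.5°C". Both late classes require that no ETF criterion was met before. ACPR is what remains: "No parasites on D28 irrespective of axillary temperature without previously meeting any of the criteria of ETF, LCF or LPF".

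The section on assessment of secondary endpoints points elsewhere: "ACPR will be determined according to the standard WHO protocol (WHO 2003". It sends the clinical and parasitological failure rates on days 3, 7, 14 and 28 to the same standard. The Definitions section cites that standard for the numbering of days but prints its own failure list.

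Under the visit schedule, the last study dose is on the evening of D2. An examination and a blood film follow on the morning of D3, and the next scheduled examination is D7.

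**The concern.** Fever with parasites, at any density, is a failure from D4 onward. On D3, after the full course of treatment, the same two findings count for nothing unless the count is still at least a quarter of baseline or the child has danger signs or severe malaria. Read literally, the list lets a child who is still symptomatic and parasitaemic after treatment pass as a success.

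The excluded range is not confined to trace counts. Entry allows 2000 to 200000 parasites/µl with a temperature of 37.5°C or more. A child who entered above 8000/µl could meet the trial's own entry thresholds for temperature and density again on D3 and still not be an ETF.

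The rates at stake are ETF and ACPR. Both are secondary endpoints, and the protocol wants efficacy information from them for planning phase III.

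**Working it through.** There is no plan figure to reproduce, because this is a question of classification logic. The inputs are the criteria quoted above, the visit schedule, the entry limits (inclusion criteria) and the arm size of 60 (sample size paragraph under selection of subjects).

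**Step 1: test one child against each rule.** Take a child on D3 with temperature ≥37.5°C, a count above 0 but below 25% of D0, no danger signs or severe malaria, and a D2 count not above D0.

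- ETF, danger signs or severe malaria: not met, since fever alone does not trigger it.
- ETF, D2 count above D0: not met.
- ETF, D3 count at least 25% of D0: not met.
- LCF: the fever route opens on D4 and the danger-sign route after D3, so neither applies.
- LPF: opens on D7 and covers only afebrile children, so it does not apply.

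The child has no failure class on D3.

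**Step 2: run through the combinations.** D3 counts of 0, 1%, 10%, 24%, 25% and 50% of D0 were crossed with fever or no fever on D3 and three later courses. This was done with the list as written, then with one added ETF line: any parasitaemia on D3 with temperature ≥37.5°C.

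| D3 finding | Later course | As written | With added line |
|---|---|---|---|
| Febrile, 1%, 10% or 24% of D0 | Films negative on D7, D14, D28 | ACPR | ETF |
| Febrile, 1%, 10% or 24% | Afebrile parasitaemia on D7 | LPF | ETF |
| Febrile, 1%, 10% or 24% | Febrile parasitaemia on D28 | LCF | ETF |
| Febrile or not, 25% or 50% | Any | ETF | ETF |
| Afebrile, below 25% | Any | Unchanged | Unchanged |
| No parasites on D3 | Any | Unchanged | Unchanged |

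Only febrile children with a count above 0 and below 25% change class. ETF is lower than it would otherwise be in all three of their later courses. ACPR is higher in the first course only.

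**Step 3: range of counts.** 25% of 200000 is 50000/µl, so a child at the upper entry limit can have any D3 count below 50000/µl without being an ETF. Setting 25% of D0 equal to the lower entry limit gives D0 = 2000/0.25 = 8000/µl. Above that baseline, a D3 count of 2000/µl or more can lie below the 25% line.

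**Step 4: size per child.** With all 60 children in an arm evaluable, one child is 1/60 = 1.7 points. As a scale only, 3 children are 3/60 = 5.0 points and 6 are 6/60 = 10.0 points. The documents give no expected count, so no total can be computed.

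**Step 5: does the schedule close the gap?** No examination is planned between D3 and D7, and the D7 visit carries a tolerance of –1 to +3 days. A child seen febrile and parasitaemic at an unscheduled visit from D4 is LCF. Guardians are told to return if the child worsens, so fever that merely persists may not be seen in that window.

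**The case against.** The strongest reply is that the printed list may be only a summary. ACPR and the failure rates are assigned to the WHO 2003 protocol. If that standard has a criterion for fever with parasitaemia on D3, these children are already failures by reference and the fault is an incomplete list. If it has none, the protocol follows the standard it names. That text is not at hand, so the documents cannot settle which is true. This part stands. A reader might infer that two conflicting rule sets are in force; nothing shows that they differ. What is shown is that the list has a gap and that the protocol does not say which source governs.

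A reader might also infer that every such child inflates ACPR. That is wrong: a child whose parasites persist or return so as to meet LCF or LPF is already outside ACPR, and only the ETF rate is then affected.

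A third tempting reading is that the gap favours a slower-clearing regimen. It could, but the documents give no clearance data by arm. Slow clearance would also remain visible in the fever and parasite clearance times, which are separate secondary endpoints.

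Finally, the primary objective is safety, the sample size rests on adverse events, and no ETF or ACPR threshold for going to phase III is set. The point should be weighed accordingly. None of this removes the gap in the list, and no other section writes out a rule that closes it.

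**Conclusion.** The point holds in limited form. Applied as printed, the Definitions leave fever with parasitaemia below 25% of D0 on D3 outside ETF, LCF and LPF. ETF is then understated by 1.7 points per such child in that arm. ACPR is overstated by the same amount only when the child meets no LCF or LPF criterion up to D28.

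This rests on three assumptions:

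- The printed list is what would be applied.
- Febrile parasitaemia after treatment is a failure, as the protocol itself treats it from D4.
- The denominator is 60 per arm.

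The total shift is unknown, and a difference between arms is not established. The documents do not support saying that these endpoints decide which combination goes forward: the stated purpose is information for judging and planning phase III, on safety as well as efficacy. It is a fault in secondary endpoint definitions that should be corrected because it is real and cheap to correct.

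**What to change.** Make three changes, to endpoint classification only:

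1. Check the failure list in the Definitions against the standard named under assessment of secondary endpoints, and resolve any difference openly.
2. Add to ETF: parasitaemia on D3 with axillary temperature ≥37.5°C. This is the threshold already used for LCF, and it leaves no gap for febrile parasitaemia between D3 and D4.
3. State one governing classification for ETF, LCF, LPF and ACPR, and refer to it in both sections. It should be reconciled with the named standard and should not silently displace it.

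The cost is about one line of definition and one cross-reference. The D3 film and examination are already scheduled. A D3 temperature is not itemised in the visit list, but fever clearance time needs serial temperatures, so it should be confirmed that it is recorded. The downside is that ETF may come out slightly higher and ACPR slightly lower. Nothing here bears on how a child is treated.

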Treating malaria with a combination of effective drugs is therefore becoming a new paradigm in malaria control, with the particular aim to delay and possibly reverse the development of drug resistance through different mechanisms (Nosten and Brasseur 2002). Artemisinin drugs in combination with a variety of partner drugs have proved highly effective in a number of field trials (International Artemisinin Study Group 2002). Although the costs for artemisinin combination therapy (ACT) are currently still higher than the price for chloroquine and pyrimethamine-sulfadoxine regimens, more and more African countries are currently switching their antimalarial first line treatment to ACT. So far no resistance to ACT has been described in vivo. Most research focuses on the use of artesunate combined with currently used standard drugs such as amodiaquine and sulphadoxine-pyrimethamine. There is evidence that combinations improve efficacy without increasing toxicity, however cure rates vary widely and depend on the level of resistance of the partner drug. New compounds with novel mechanisms of action and a short half-life to prevent resistance are therefore urgently needed to protect such ACT. The combination of the two short acting drugs methylene blue and artesunate or the combination of methylene blue with the long-acting and still sufficiently effective AQ ought to be considered as a possible solution to this problem in SSA (Akoachere et al. 2005, Barker et al. 2005).

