# Trial objectives and purpose

The purpose of the study is to investigate the safety and efficacy profile of the combinations MB-AS and MB-AQ in comparison with AS-AQ in African children with uncomplicated falciparum malaria.

The primary objective of this study is:

- To investigate the safety of the combinations MB-AS and MB-AQ in children with uncomplicated malaria caused by *Plasmodium falciparum*

Justification: MB, AS, AQ and AS-AQ have been shown to be safe in the target population. However, to treat children with the combination of MB-AS or MB-AQ is new. Thus, all adverse events of these new combinations are of interest. The comparison with AS-AQ, the new official first-line treatment for uncomplicated malaria in Burkina Faso, will help to judge the safety of MB-AS and MB-AQ in the study population. This trial should give the necessary information about the safety of the combination MB-AS and/or MB-AQ for judgment and planning of future phase III trials.

The secondary objective of this study is:

- To investigate the efficacy of MB-AS and MB-AQ

Justification: The combination MB-chloroquine has been shown to be effective against malaria in the Nouna study population. However a high rate of recrudescences was observed due to high background resistance to CQ (Meissner, unpublished). Therefore alternative drug combinations with MB need to be identified. There is now sufficient evidence from in vitro and animal models for existence of synergy between the two short acting drugs MB and AS (Akoachere et al. 2005, Barker et al. 2005). Thus AS seems to be an ideal partner drug to MB but it remains to be shown that MB-AS is sufficiently safe and effective when given over a period of three days. Alternatively, the combination MB-AQ could still be sufficiently effective even in areas of high resistance against chloroquine. This trial should give the necessary information about the efficacy of the combinations MB-AS and MB-AQ for judgment and planning of future phase III trials.

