# Definition of outcomes

Primary endpoint:

- Incidence of observed and self-reported non-serious adverse events over the 28 days observation period (definition chapter 11)

Secondary endpoints:

- Incidence of serious adverse events (definition: chapter 11) over the 28 days observation period
- ACPR rate until D28
- Early treatment failure (ETF) rate
- Late clinical failure (LCF) rate at D14 and D28
- Late parasitological failure (LPF) rate at D14 and D28
- Fever clearance time
- Parasite clearance time
- Change in haematocrit after 2, 3, 7, 14 and 28 days compared to baseline

*Justification:* SAE rates and clinical and parasitological failure rates as well as fever and parasite clearance times are standard endpoints to judge the safety and efficacy of antimalarial drugs. This information will be relevant to plan future phase III trials.

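### ACPR, LCF and LPF count new infections as treatment failures and the planned PCR genotyping feeds no listed endpoint, so ACPR as a measure of cure is expected to be biased against MB-AS, by an unknown amount

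*Protocol*

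**What the plan says.** All references are to the Protocol.

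- **Definitions.** LCF includes "Presence of parasitemia + axillary temperature ≥37.5°C on any day from D4 to D28, without previously meeting any criteria of ETF". LPF is "Presence of parasitemia on any day from D7 to D28 + axillary temperature <37.5°C, without previously meeting any of the criteria of ETF". ACPR is "No parasites on D28 irrespective of axillary temperature without previously meeting any of the criteria of ETF, LCF or LPF". None of the three has a PCR condition. The same table defines recrudescence and reinfection by genotyping; reinfection is "New infection from D14 to D28 according to PCR genotyping", and recrudescence has the same window.
- **Definition of outcomes.** Efficacy is listed as "ACPR rate until D28", the ETF rate, LCF and LPF rates at D14 and D28, and the two clearance times. No PCR-corrected rate and no recrudescence rate is listed. The Protocol summary and the parameter list in Assessment of secondary endpoints do not add one.
- **Assessment of secondary endpoints.** "Differentiation of recrudescences from new infections will be achieved by comparing PCR-generated" msp1 and msp2 patterns, using paired isolates from admission and from the day parasites reappear. ACPR and the failure rates are referred to the WHO 2003 protocol, with no mention of a correction.
- **Visits and treatment schedule.** Filter papers are kept at D0, at D7, D14 and D28, and at any unscheduled return between D3 and D28.
- **Trial objectives and purpose.** On the earlier methylene blue-chloroquine work: "However a high rate of recrudescences was observed due to high background resistance to CQ". This is the stated reason for looking for another partner drug.

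**The concern.** In this setting a D28 rate based on any parasitaemia combines two things: cure of the treated infection, and freedom from a new one during follow-up. The second depends on how long the drugs stay active. The introduction describes "the combination of methylene blue with the long-acting and still sufficiently effective AQ" and calls methylene blue and artesunate short acting. MB-AQ and AS-AQ contain amodiaquine and MB-AS does not. Enrolment is in the rainy season in an area that the summary describes as having high transmission intensity. New infections are therefore expected to lower ACPR more in MB-AS than in the other two arms, even if all three cure equally well.

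The trial was prompted by recrudescence, and its efficacy results are meant to inform the planning of phase III. With the endpoints as listed, a combination that fails to cure cannot be told from one that cures but gives no later protection. The samples that would separate them are being collected.

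**Working it through.** **The plan's own figures.** The protocol gives no expected ACPR, reinfection risk or power for efficacy. Its one reproducible calculation concerns adverse events. Rates of 25%, 25% and 5% have mean 0.183 and variance 0.0089, and a three-group 5% chi-square test then needs 54.1 per group for 80% power, against the stated 54. That calculation is sound but has no bearing here.

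**Step 1: how a new infection is classified.** Take a child who clears parasites and acquires a new strain found at D28. Without fever the child meets LPF; with fever, LCF. Either way ACPR is lost. Genotyping would label the case a reinfection, but no endpoint refers to that label.

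**Step 2: direction and size.** Let C be the true cure rate, equal in all arms. Let r be the risk of a new infection by D28 without amodiaquine, and s the share of that risk which amodiaquine prevents. The documents give none of the three, so all are assumptions. Treating cure and new infection as independent:

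- MB-AS: uncorrected ACPR = C(1 − r)
- amodiaquine arm: uncorrected ACPR = C(1 − r(1 − s))
- gap = C·r·s

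| C | r | s | MB-AS | AQ arm | Gap (points) |
|---|---|---|---|---|---|
| 90% | 10% | 50% | 81.0% | 85.5% | 4.5 |
| 90% | 10% | 100% | 81.0% | 90.0% | 9.0 |
| 90% | 20% | 50% | 72.0% | 81.0% | 9.0 |
| 90% | 20% | 100% | 72.0% | 90.0% | 18.0 |
| 80% | 10% | 50% | 72.0% | 76.0% | 4.0 |
| 80% | 10% | 100% | 72.0% | 80.0% | 8.0 |
| 80% | 20% | 50% | 64.0% | 72.0% | 8.0 |
| 80% | 20% | 100% | 64.0% | 80.0% | 16.0 |

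True cure is equal in every row, so the whole gap comes from new infections. It is zero if r = 0 or s = 0. At r = 5% it is 2.0 to 4.5 points; at r = 30%, 12 to 27 points.

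For scale only: with 60 per arm, a two-group 5% chi-square test would call the gaps in the table significant in about 7% (72% v 76%) to 72% (72% v 90%) of trials. The protocol specifies no such test for ACPR.

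**Step 3: what correction does.** A Kaplan-Meier estimate that censors new-genotype reappearances recovers C in each arm if new infection is independent of recrudescence. Dropping newly infected children from a simple proportion is slightly less clean. If every uncured child is classed as recrudescent, the result is C(1 − r)/(1 − C·r). For C = 90% and r = 20% this is 0.72/0.82 = 87.8%, against 90% in an arm with no new infections. For C = 80% and r = 20% it is 0.64/0.84 = 76.2%, against 80%. So a gap of 18 points shrinks to 2.2, and one of 16 points to 3.8.

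**Step 4: the windows.** LCF can be met from D4 and LPF from D7, and filter papers are taken at D7 and at unscheduled returns after D3. Recrudescence and reinfection are defined only from D14. A reappearance between D4 and D13 is a failure with a sample, but has no PCR class.

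**The case against.** **Genotyping is not unattached, and the rest may be in the SAP.** It is described under the methods for the secondary endpoints, and WHO 2003 is cited for ACPR. A reader might infer that the genotypes will go unused. The documents do not show that; they show only that no listed endpoint depends on them. The objection does not remove the point, because the Definitions table is a stated rule that makes any late parasitaemia a failure. An analysis plan could add a corrected rate, but the endpoints as written do not contain one.

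**Uncorrected ACPR is a legitimate endpoint.** This stands. It measures freedom from parasites through follow-up, and protection after treatment has value of its own. The fault is that it is the only ACPR defined.

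**The size is assumption throughout.** This also stands. The introduction's remark that children have several malaria episodes a year concerns sub-Saharan Africa in general, not Nouna. The cited fall from 92% cured at D14 to 72% at D28 comes from artesunate monotherapy in Gabonese children aged 4-15, and the protocol does not say how much of it was new infection. Neither fixes r.

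**The impact is limited.** ACPR is a secondary endpoint in a pilot trial with a safety primary. The retained samples also mean that a corrected rate could be produced later. That is true, but choosing between corrected and uncorrected results after seeing the data is what prior definition avoids.

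**Conclusion.** The point holds as a defect of endpoint definition. New infections count as failures under LCF, LPF and ACPR, and the genotyping planned to identify them enters no listed endpoint. As a measure of cure, uncorrected ACPR is expected to be biased against MB-AS. That direction rests on the protocol's own description of the drugs, season and transmission.

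The gap of about 4 to 18 points is illustrative. It assumes equal cure of 80-90%, new infections of 10-20% in MB-AS and none to half as many in the amodiaquine arms, and independence of cure and new infection.

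A reader might go further and conclude that MB-AS will look worse than it is, or that a false significant difference is likely. The documents support neither: they give no local reinfection risk, no duration of amodiaquine protection, no MB-AS cure rate and no test of ACPR. The primary safety comparison is untouched. MB-AQ against AS-AQ is little affected because both contain amodiaquine, although new infections can lower the absolute rates in every arm.

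**What to change.** In Definitions, Definition of outcomes and Assessment of secondary endpoints:

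1. Keep the uncorrected ACPR, LCF and LPF rates, labelled as such. Add a PCR-corrected set and the recrudescence rate per arm as secondary endpoints. No new main efficacy endpoint is needed.
2. State that a reappearance with a new genotype is not a failure. Either censor it on that day in a Kaplan-Meier estimate of PCR-corrected cure at D28, or exclude it from the denominator of a simple proportion. Name one. The Kaplan-Meier estimate leaves less residual bias in the model above.
3. Count recrudescent reappearances as failures. State how undetermined PCR results are handled (for example, as failures), with a sensitivity analysis that treats them the other way.
4. Align the recrudescence and reinfection window, now D14-D28, with the LCF and LPF windows and with the sampling at D7, D14, D28 and unscheduled visits after D3. If reappearance before D14 is to be treated as recrudescence without genotyping, say so.

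The cost is wording and one named estimator, since samples and genotyping are already planned. The downsides are slightly wider intervals, more censoring or exclusion in MB-AS than in the other arms, and some genotyping misclassification. Reporting both sets of rates side by side lets readers judge these.
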